#### Specific aim 4: identify a prediction model of treatment response in youth with anxiety disorders

GWAS data for general susceptibility for major psychiatric illnesses (such as adult and youth anxiety, MDD, ADHD, and others), and antidepressant treatment response [146] will be used to train GRPS in the GAYA study sample. For each of these GRPS the amount of variation explained in the clinical response of youth receiving Breathe will be assessed. It will also be evaluated how much of this variation can be explained by clinical symptoms/vulnerability markers and subsequently whether the combination of these measures (i.e., GRPS plus clinical symptoms/vulnerability markers) can increase our ability to predict clinical response in youth with anxiety disorders. Further, explorative GWAS will be conducted in two datasets: (a) 3,000 youth recruited to receive CBT and (b) around 10,000 individuals (all age groups, including the 3,000 youth) by combining the GAYA study sample with samples available via collaborations [52, 61].

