## Methods

### Aims

In the current article we outline the design and methods of the GAYA study that aims to better understand the genetic underpinnings of anxiety disorders in Canadian youth. The GAYA study will help close the above-identified gaps in existing research in youth anxiety through a framework of integrated specific aims that will enhance our understanding of the specific genetic contributions to anxiety from childhood through adolescence, and implications for treatment. The specific aims and hypotheses are outlined in Table 1.

**Table 1 Tab1:** Specific aims and hypotheses

	Specific Aim	Hypothesis
**1**	Identify genetic risk factors associated with clinical symptoms and vulnerability markers of youth anxiety.	Each clinical symptom and vulnerability marker will be associated with common genetic variations.
**2**	Identify genetic factors that are unique to anxiety in different age groups.	If the overlap in genetic risk factors is partial between different age groups, then the non-overlapping part will be driven by associations with common genetic variants.
**3**	Identify genetic factors that are shared and unique between anxiety and its common comorbidities.	If pleiotropy is driving co-occurrence of anxiety and common comorbidities, then these traits will have shared genetic risks.
**4**	Identify a prediction model of treatment response in youth with anxiety disorders.	Response to CBT in youth anxiety will be predicted using data from common genetic variation, clinical symptoms, and vulnerability markers.

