#### Core questionnaires

The demographic questionnaire will be designed by the study team to gather information about the youth’s age, sex assigned at birth, gender, socioeconomic status, ethnicity, education, lifetime diagnoses of mental health disorders, and current/past mental health treatment history.

To assess anxiety symptoms, the study will use the Screen for Child Anxiety Related Emotional Disorders (SCARED [66]), validated for youth ages 9–18, which assesses symptoms of panic, GAD, separation anxiety, and social anxiety disorder, over the past 3 months. Each of the 41 items will be rated on a 3-point scale ranging from 0 to 2 (0 = hardly ever true, 1 = sometimes true, 2 = often true). The SCARED has high sensitivity (82%) and moderate specificity (52%), and acceptable-to-excellent internal consistency (α = 0.89–0.94), test-retest reliability (ICCs 0.59–0.86), reasonable convergent validity with anxiety measures, and discriminant validity [66–69].

Depression symptoms will be measured using the Short Mood and Feeling Questionnaire (SMFQ), a short version of the MFQ [70] validated for youth ages 6 and up, which was developed to briefly evaluate depressive symptoms in youth over the past 2 weeks [71]. The SMFQ consists of 13 items. Each item will be rated on a 3-point scale ranging from 0 to 2 (0 = not true, 1 = sometimes true, 2 = true). The SMFQ has high specificity (83%) and moderate sensitivity (71%), and acceptable-to-excellent internal consistency (α = 0.83–0.92), test-retest reliability (ICCs 0.61–0.80), and reasonable convergent validity with other depression measures [72–76].

Post-traumatic stress disorder (PTSD) symptoms will be measured using the CPSS-SR-5, validated for youth ages 8–18. It is a modified version of Child PTSD Symptom Scale self-report (CPSS-SR) [77] for DSM-5. The 20 PTSD symptom items will be rated over the past month on a 5-point scale of frequency and severity from 0 (not at all) to 4 (6 or more times a week/severe). The CPSS-SR-5 has excellent internal consistency for total symptom severity (α = 0.92), good test-retest reliability (*r* = 0.80), and high sensitivity (93%) and specificity (82%) for a probable diagnosis of PTSD. The CPSS-SR-5 also demonstrates convergent validity with the CPSS-I-5 interview(*r* = 0.90) [77–79].

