### Optional intervention

#### Intervention procedures

Youth enrolled in GAYA who are ages 13–19, not currently in mental health treatment, and do not endorse psychosis screening questions will be offered the opportunity to participate in a self-managed Internet-based CBT (iCBT) program, Breathe (Being Real, Easing Anxiety: Tools Helping Electronically) [114], at all recruitment sites. These youth will be linked to the Strongest Families Institute (SFI, http://strongestfamilies.com/), where all referred youth will receive the Breathe program that is part of SFI’s validated eplatform IRIS (Intelligent Research and Intervention Software).

Through weekly self-managed check-ins, during which youth assess and rate their social-emotional functioning over the past week, a detailed monitoring of anxiety symptoms over the course of the Breathe program will be enabled. Youth will also be asked to rate their anxiety symptoms based on the SCARED pre-, post-treatment, and at a 3 months follow-up. Intervention response will be defined as the changes in SCARED scores from pre- to post-treatment for the 3 months follow-up.

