#### Breathe intervention description

Breathe is a self-mediated 6-module standardized iCBT program that involves: (a) multimedia-based education about anxiety problems and approaches to overcoming anxiety (e.g., reviewing why exposure exercises are important); (b) self-assessment activities to determine level of intervention and safety needs; (c) activities that teach users about anxiety sensitivity and how to develop realistic thinking about anxiety-producing situations; (d) activities for practicing coping and relaxation skills; (e) development of a hierarchy of feared situations and steps for gradual and repeated exposure to feared situations (using imagery/in vivo activities); (f) contingency management (examining the function of anxiety from a reinforcement perspective) and modelling (viewing videos of others confronting feared situations); and (g) skills for maintenance and relapse prevention. Animations, embedded videos, timed prompts, and on-screen pop-ups are used in each module to provide an interactive and multimodal experience. In one of the largest effectiveness trials of iCBT in adolescents conducted to date, that used SFI’s IRIS eplatform, 563 adolescents aged 13–19 were randomly assigned to 6 weeks of Breathe (*n* = 280) or to visit a static (no elements of interactivity or personalization) website which provided resources for anxiety (*n* = 283) [115]. In the trial, adolescents who participated in Breathe had a greater improvement in symptoms 3 months after program use (*p* = 0.04) [115]. Although this Breathe study was complimented by one telephone coach support session to those who wanted the additional support, the current study will only be self-mediated.

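### Aim 4 measures response as SCARED change and then credits clinical symptoms with explaining it: if pre-treatment SCARED is among them, regression to the mean can pass as prediction of CBT response

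*Protocol article*

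**What the plan says.** All references are to the protocol article.

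- **Outcome.** Under Intervention procedures: "Intervention response will be defined as the changes in SCARED scores from pre- to post-treatment for the 3 months follow-up". SCARED is taken three times: "Youth will also be asked to rate their anxiety symptoms based on the SCARED pre-, post-treatment, and at a 3 months follow-up". No adjustment of the change for its starting value is stated.
- **Predictors.** Under Specific aim 4, each GRPS is first assessed for the variation in response that it explains. Then: "It will also be evaluated how much of this variation can be explained by clinical symptoms/vulnerability markers". The last step asks "whether the combination of these measures (i.e., GRPS plus clinical symptoms/vulnerability markers) can increase our ability to predict clinical response".
- **Claim.** The Aim 4 hypothesis in Table 1 reads: "Response to CBT in youth anxiety will be predicted using data from common genetic variation, clinical symptoms, and vulnerability markers".
- **What clinical symptoms can mean.** Under Core questionnaires, SCARED is the study's anxiety symptom measure, with "test-retest reliability (ICCs 0.59–0.86". Under Specific aim 1, the SCARED subscales are listed among the anxiety phenotypes. Specific aim 4 names no instrument.
- **Covariates.** The Data analysis strategy gives age, sex, gender and recruitment procedure or site as examples. Baseline SCARED is not among them, but the list is open.
- **Comparison.** Every referred youth receives Breathe. No untreated group is described for Aim 4.

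**The concern.** A change score contains the pre-treatment score with a negative sign. If that score, or a subscale of it, is also a predictor, its error appears on both sides and creates a negative correlation that has nothing to do with treatment. Youth who scored high partly by chance seem to improve, and those who scored low partly by chance seem to worsen.

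The R² credited to clinical symptoms, and the total R² of the combined model, would then mix this artefact with any real prediction. The comparison of symptoms with GRPS would also be uneven, because only the symptom side gains. With no untreated group, neither regression to the mean nor natural course can be estimated and subtracted, yet Table 1 words the result as prediction of response to CBT. The Discussion presents the treatment prediction models among the study's contributions and expects results to inform personalization of care.

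**Working it through.** The article gives no R², effect size or power figure for Aim 4, so there is no stated figure to reproduce. The check asks how much change-score variance pre-treatment SCARED explains when response does not differ between youth.

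**Inputs**
- Reliability ρ = 0.59 to 0.86, the SCARED test-retest ICCs under Core questionnaires.
- n = 3,000 youth receiving CBT, from Specific aim 4.
- Assumptions: equal pre and post variances (set to 1), independent errors, and the ICC standing in for the pre-post correlation. The retest interval is not given.

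**1. No true difference in response.** Let pre = T + e₁ and post = T + e₂, with var(T) = ρ and error variance 1 − ρ.
- var(post − pre) = 2(1 − ρ); cov(pre, post − pre) = −(1 − ρ)
- correlation = −√((1 − ρ)/2); R² = (1 − ρ)/2; slope = −(1 − ρ)

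| ρ | correlation | R² | expected change at +1 SD baseline |
|---|---|---|---|
| 0.59 | −0.453 | 0.41/2 = 20.5% | −0.41 SD |
| 0.86 | −0.265 | 0.14/2 = 7.0% | −0.14 SD |

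A simulation (n = 3,000, 400 replicates) gave R² of 20.5% and 7.0%. The mean absolute t for pre-treatment SCARED was about 28 and 15, so the artefact would look like a firm result.

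**2. True response varies** with SD h (in observed-score SDs, assumed, unrelated to true baseline): R² = (1 − ρ)² / (2(1 − ρ) + h²).
- ρ = 0.59: h = 0.5 gives 0.1681/1.07 = 15.7%; h = 1.0 gives 0.1681/1.82 = 9.2%.
- ρ = 0.86: h = 0.5 gives 0.0196/0.53 = 3.7%; h = 1.0 gives 0.0196/1.28 = 1.5%.

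**3. Separate enrolment SCARED as predictor**, with independent error: simulated R² = 0.0003 at both reliabilities. The artefact disappears.

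**4. GRPS.** Take a GRPS related only to true severity (assumed r = 0.2), with no effect on response.
- Alone against change: R² = 0.0003, so no artefact.
- With pre-treatment SCARED in the model: mean t of 4.4 (ρ = 0.59) and 2.9 (ρ = 0.86). Pre-treatment SCARED measures severity with error, and the GRPS picks up part of the severity that it misses.
- In the combined model R² on change rises from 0.2049 to 0.2101 and from 0.0697 to 0.0725, increments of 0.0052 and 0.0028.
- With pre-treatment SCARED in the model, the GRPS coefficient is the same whether the outcome is change or the post score (difference 0.000).

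So the shared-error artefact lies in the R² credited to baseline SCARED and in the total R² of the combined model. Adjusting for baseline brings a different, smaller distortion into the genetic terms.

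**The case against.** **The premises are partly inferred, and this stands.** Specific aim 4 names no instrument. The core questionnaires are completed in REDCap at the study sites, while Breathe runs on a separate platform with its own pre-treatment SCARED. Two administrations are therefore a natural reading. A reader might infer that 7.0% to 20.5% will certainly appear in the results. The text does not support that: the figures are a ceiling for one reading, and step 3 gives about zero for the other. Coupling is also weaker for SMFQ, BIS/BAS and the tasks than for SCARED itself.

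**The article is condensed and its covariate list is open.** A full analysis plan may adjust for baseline, and validation detail belongs there. This stands for the missing detail. It does not remove the point, because the article itself fixes the response definition, the variance-explained analysis and the CBT-response hypothesis.

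**Two stronger readings fail.** A reader might infer that the combined model must look better simply because R² in a fitted sample rises with each added predictor. The article does not say that performance is judged in the fitted sample. A reader might also infer from the earlier Breathe trial that most pre-post change is not specific to CBT. From p = 0.04 with 280 and 283 youth, z of about 2.054 × √(1/280 + 1/283) gives about 0.17 SD, if all were analysed. But the comparator was a website with anxiety resources, and the article reports no pre-post change against which to set that figure.

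**Baseline adjustment is not free.** This also stands. Step 4 shows that it can make variants linked only to severity look associated with outcome, so it should not be compulsory in every GRPS model and GWAS.

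**Conclusion.** The point holds in a conditional form. Response is fixed as a SCARED change, clinical symptoms are then credited with explaining it, and there is no untreated group. If pre-treatment SCARED or its subscales are among those symptoms, shared error alone gives them up to 20.5% (ICC 0.59) to 7.0% (ICC 0.86) of change-score variance, less where true response varies and about zero for an independent enrolment SCARED. This assumes equal pre and post variances and the stated ICCs as the pre-post correlation; more error than the ICCs imply would raise the figure.

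Whichever administration is used, a single-arm analysis cannot separate prediction of natural course from prediction of response to CBT. A baseline score can validly forecast change. The fault is in calling that forecast response to treatment.

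**What to change.** - **State the predictor and the endpoint.** Say whether the SCARED used as a predictor is the enrolment or the pre-treatment administration, and whether response runs to post-treatment or to 3 months; the present definition can be read either way.
- **Symptom and combined models.** Use follow-up SCARED as the outcome, with pre-treatment SCARED in the reference model. Report the incremental R² of the other symptoms, the vulnerability markers and the GRPS over that reference. Do not count the baseline SCARED term as prediction of response: under the assumptions of step 1 it would account for ρ² of follow-up variance (0.59² = 35% to 0.86² = 74%) through stability of severity alone.
- **GRPS-only models and exploratory GWAS.** Report results with and without baseline adjustment, and note that an association seen only after adjustment may reflect severity.
- **Wording.** State the Aim 4 hypothesis and conclusions as prediction of anxiety outcome after Breathe, not of response to CBT.

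Pre-treatment SCARED is already to be collected, so no new data are needed. The cost is a smaller reported R² and one extra set of models. The missing comparison group remains a limit of the design that analysis cannot remove, which is why the wording has to change as well.

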#### Specific Aim 2: identify genetic factors that are unique to anxiety in different age groups

Multi-trait conditional and joint analysis [138] to adjust GWAS summary statistics from the GWAS in youth for the genetic effects in adult anxiety to identify putative age group-specific SNP associations. It is noteworthy that previous analyses in closely related traits of similar sample size (e.g., ADHD) were able to identify new genome-wide significant hits specific to the traits under analysis [138]. Similarly, summary statistics from youth and adult anxiety GWASs will be analysed with ccGWAS [139], a tool designed to identify loci with different allele frequencies among different trait groups. Using ccGWAS genetic loci will be identified that are specific in their association to the individual age groups.

Using established protocols (SBayesR [140]/LDpred2 [141]/PRSice2 [142]) genomic risk profile scores (GRPS) will be generated in the GAYA study sample trained on discovery datasets from different age groups (i.e., pairwise between the youth and adult GWAS) to assess the variance explained through genetic liability for anxiety disorders in one age group for the other. Finally, where appropriate, CLiP [143] will be used to study heterogeneity in GRPS for the GAYA study sample.

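### Aim 4 names variation explained in the Breathe youth as its only criterion, with no separate evaluation sample, and does not say that those youth are left out of the youth-anxiety GWAS behind one of its scores

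*Protocol article*

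**What the plan says.** Table 1 of the protocol article states Aim 4 as a prediction aim: "Identify a prediction model of treatment response in youth with anxiety disorders". The Aim 4 paragraph of the data analysis strategy says that GWAS data on psychiatric illness, "such as adult and youth anxiety, MDD, ADHD, and others", and on antidepressant response "will be used to train GRPS in the GAYA study sample". It then gives the measure: "For each of these GRPS the amount of variation explained in the clinical response of youth receiving Breathe will be assessed". The same is to be done for clinical symptoms and vulnerability markers, and finally for both together, to see whether the combination "can increase our ability to predict clinical response in youth with anxiety disorders".

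Four other places bear on this:

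- **Optional intervention, Intervention procedures:** response is change in SCARED score.
- **Aim 1:** SCARED subscales are among the GWAS phenotypes, and GAYA results are meta-analysed with other available samples.
- **Aim 2:** three score-building tools are listed without choosing one, and scores "will be generated in the GAYA study sample trained on discovery datasets from different age groups".
- **Aim 4, last sentence:** exploratory GWAS are planned in 3,000 youth recruited to receive CBT and in about 10,000 individuals who include those 3,000.

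**The concern.** A prediction claim needs performance in people who did not shape the model. Aim 4 names one criterion and one group with Breathe response data. The larger set contains the same youth and is named for exploratory GWAS, not for validation. Two kinds of optimism could follow.

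The first is ordinary. The regression coefficients, and any choice of score method or threshold made on response, would be fitted to the youth in whom variation explained is then reported.

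The second comes through the score weights. If the youth-anxiety GWAS used for scoring contains GAYA, each treated youth's SCARED has contributed to the weights applied to that youth's own genotype. The score then partly encodes that youth's own SCARED level. Because SCARED level is related to later SCARED change, the score can look predictive of response with no genetic signal present.

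At stake is Aim 4's conclusion on whether genetic data help to predict response to CBT. The Discussion expects the study's results to inform personalization of care.

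**Working it through.** The article gives no R2, power or sample-size figure for Aim 4 beyond the 3,000, so there is no stated figure to reproduce. Both checks below rest on assumptions, which are marked.

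**1. Ordinary optimism.** When k uninformative scores join p predictors with baseline R2 = R2b in n youth, the expected rise in unadjusted in-sample R2 is (1 − R2b) × k / (n − p − 1).

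- From the article: n = 3,000.
- Assumed: p = 15, R2b = 0.10, k = 5 (youth anxiety, adult anxiety, MDD, ADHD and antidepressant response; the article leaves the list open), and smaller n in case fewer youth supply post-treatment or follow-up SCARED.

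Results:

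- n = 3,000: 0.90 × 5 / 2,984 = 0.0015
- n = 600: 0.90 × 5 / 584 = 0.0077
- n = 300: 0.90 × 5 / 284 = 0.0158

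A simulation with 300 runs per setting (1, 5 or 10 null scores; n = 3,000, 600 or 300) showed how often useless scores appear to help:

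| Criterion | Runs showing a gain |
|---|---|
| Unadjusted in-sample R2 | 100% |
| Adjusted R2 | 28% to 49% |
| Nested F test, p < 0.05 | 3% to 6% |
| 10-fold cross-validated R2 | about 2% to 19% |

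The mean cross-validated change for five null scores was −0.0018 at n = 3,000 and −0.019 at n = 300.

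Tuning on response adds to this. Taking the best of 11 correlated score thresholds (assumed correlation 0.7 between neighbours) gave p < 0.05 in about 32% of null runs, with mean R2 0.001 at n = 3,000 and 0.011 at n = 300.

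**2. Overlap.** Take a trait with no genetic signal, M independent effective SNPs, discovery size N, and an unshrunk score using all SNPs. For a person inside the discovery set, the score equals (M/N) times that person's own phenotype plus noise with variance of about M/N. The squared correlation of score with own phenotype is therefore M/(M + N). If the phenotype is pre-treatment SCARED, with pre–post correlation r and equal variances, the squared correlation of pre-treatment SCARED with change is (1 − r)²/[2(1 − r)] = (1 − r)/2. Spurious R2 for SCARED change is the product of the two.

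- From the article: N = 13,000 (GAYA alone).
- Assumed: N = 60,000 (after meta-analysis), M = 50,000, r = 0.5, and enrolment SCARED standing for pre-treatment SCARED.

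Results:

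- N = 13,000: 50/63 × 0.25 = 0.794 × 0.25 = 19.8%
- N = 60,000: 50/110 × 0.25 = 0.455 × 0.25 = 11.4%
- With r = 0.7 instead, the second factor is 0.15, giving 11.9% and 6.8%

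A simulation scaled down tenfold with 300 treated youth and r = 0.5 gave 19% and 11%, in line with the formula. With the treated youth left out of discovery, the score explained 0.2% to 0.3%, which is chance level (1/299 = 0.33%). With enrolment SCARED already in the model, the increment from the overlapping score also fell to 0.3%. So overlap mainly damages the score-by-score result. Cross-validation within the Breathe youth would not remove it, because the weights are fixed before the folds are drawn.

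**The case against.** A reader might infer that the plan evaluates the model in the youth it was fitted to, and that genetic scores will therefore always appear to improve prediction. The document supports neither statement. It never says that evaluation is in-sample or that R2 is unadjusted, and validation detail may well sit in a full protocol or analysis plan that is not shown. The guaranteed rise belongs to unadjusted in-sample R2 only. Adjusted R2, a nested test or cross-validation would not rise by construction, and none of these is ruled out.

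Other points also stand. Score weights come from GWAS of illness and of antidepressant response, not from Breathe response, so only a few coefficients and any tuning would be fitted to it. At 3,000 youth the ordinary optimism is negligible. The three scoring tools are listed under Aim 2, and nothing says that the best performer on response will be picked. Overlap is conditional too: Aim 4 does not say that the GAYA-inclusive meta-analysis supplies the youth weights, and only one score would be affected.

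What remains is that the article does choose a criterion for its prediction aim, and as stated that criterion gives no out-of-sample answer to the question asked. It also places GAYA in the youth GWAS, lists youth-anxiety GWAS data as a score source, and tests the result on change in the same scale, with no leave-out mentioned. That comes from what the text states in three places, not from brevity alone.

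**Conclusion.** The point holds in a limited form. As written, Aim 4 gives one criterion, one response sample and no separate evaluation sample, so an apparent gain from genetic scores could be optimism.

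For a handful of prespecified scores the size is minor at 3,000 youth, about 0.15 percentage points. It rises to about 0.8 points at 600 and 1.6 at 300, and further if scores are tuned on response. Those figures assume 15 clinical predictors, a baseline R2 of 0.10 and five null scores.

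The larger risk is overlap in the youth-anxiety score: roughly 11% to 20% of SCARED change explained under a complete null at r = 0.5, and 7% to 12% at r = 0.7. It arises only if the youth GWAS includes the treated youth. The sizes also rest on an unshrunk, unthresholded score and 50,000 effective SNPs, and shrinkage or thresholding would change them. The change is worth making because it is cheap and because the score-by-score results would otherwise be hard to interpret.

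**What to change.** In the Aim 4 paragraph, or in the analysis plan it relies on:

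1. Make the Aim 4 result the cross-validated R2 of genetic scores plus clinical markers minus that of clinical markers alone. Include pre-treatment SCARED among the clinical markers.
2. Do any choice of scoring method, threshold or tuning setting inside the folds, or fix it beforehand.
3. Derive the youth-anxiety score from a GWAS that leaves out the Breathe participants, and say so. This is needed as well as step 1, because folds drawn among the treated youth do not undo overlap in the weights.

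The cost is analysis code and one extra leave-out GWAS run. The reported R2 will be lower. The youth score will be slightly weaker, since up to 3,000 of 13,000 GAYA participants (3,000/13,000 = 23%) leave that discovery set, a smaller share once other samples are meta-analysed. The full-sample GWAS can still be used for Aim 1.
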